### Economic evaluation

As part of the feasibility study, methods will be trialled for capturing:i)The resources required to deliver the intervention. This will be assessed via participant-level CRFs and discussion with the intervention developers and providers. This is expected to include staff time (e.g., OT, PT, RSW), travel, training, supervision and materials.ii)Health, social and wider care service resource use. Data will be collected via a proxy Resource Use Questionnaire (RUQ). Items from the CORE Items for a Standardized Resource Use Measure (ISRUM) will be included in the RUQ, which will also draw on measures in the Database of Instruments for Resource Use Measurement [37, 38].iii)Health economic outcomes relating to health-related quality of life and wellbeing. Summaries of EQ-5D-5L [39] and EQ-5D-5L Proxy Version 2 (carers), DEMQOL and DEMQOL-proxy (carers), ICECAP-O, and ICECAP-A (carers) data will be reported.

### Embedded process evaluation

An embedded process evaluation will be conducted to examine implementation, mechanisms of impact and context of the intervention. It will be structured using the logic model, based on the programme theory developed from the initial realist review and realist qualitative study.

Healthcare support workers delivering the intervention will complete a CRF at each intervention session to document the activities undertaken by the participant, any issues with completing the session and the time spent undertaking the intervention. In addition, a purposive sample of 15–20 intervention sessions will be audio-recorded by the RSW using an encrypted audio-recorder. The audio-recordings will be used to assess the intervention delivery against a fidelity checklist to ensure treatment fidelity and assess the intervention approach. This will ensure that the intervention is tailored and personalised to individual needs, preferences, abilities and that it actively involves the participation of the carer.

Participants and healthcare professionals will be invited to take part in qualitative interviews. Qualitative data will be collected by the study qualitative researcher who will be a university employee and not involved in the delivery of the intervention:In-depth, semi-structured qualitative interviews will be conducted with 15–20 participant/participant-carer pairs, sampled purposively to include individuals with diverse characteristics. Participants will be interviewed once for up to 60 min via telephone or online shortly after the intervention.In-depth, semi-structured interviews will be conducted with 20–24 professionals in three participating sites, by telephone or online. Professionals will be sampled to include the range of roles involved in planning and delivery of services in order to inform the potential scalability of the intervention.

Interviews will explore fidelity, acceptability, intervention recruitment and retention, mechanisms of impact, views about the optimal dose of the intervention, and contextual factors affecting the intervention. This information will refine the intervention theory developed previously and inform the design for the definitive trial. Qualitative data will be analysed using realist methods with NVivo The analysis will be conducted in several stages, first deductively coding whole or partial CMOCs (context, mechanism, outcome configurations) from previous programme theory and also using inductive coding to refine CMOCs. CMOCs will then be grouped and refined and used to refine the programme logic model. Findings will be compared between participants with and without a dementia diagnosis. Quantitative data on reach, retention, fidelity and dose will also be collected and summarised using descriptive statistics in Excel, SPSS or a database programme such as Access. The process evaluation findings will then be integrated using a triangulation strategy across the various datasets by two members of the qualitative research team. We will use one or more triangulation tables to display cases (individuals, sites) in rows and categories (e.g. fidelity, acceptability) in columns. Categories will be developed based on key areas of interest for the process evaluation but will also be constructed inductively drawing on emerging study findings. Cells in the table will be populated with both qualitative and quantitative findings. The tables will then be explored to identify patterns within cases (rows) and categories (columns) and to also examine the relationships between different cases and categories. Patient and Public Involvement and Engagement (PPIE) panel members will be invited to provide comments and feedback.

In addition, we will undertake regular iterative revision of the intervention during the intervention period using a Participatory Action Research approach [40]. Therapists and RSWs will be asked to join an online focus group every 6 weeks to reflect on their experience of the intervention so far. Therapists will discuss the feasibility and acceptability of the intervention and their ideas for developing it, including any factors which might affect fidelity in the main trial. Emerging findings from participant interviews will also be discussed in the focus groups, as well as ongoing quantitative findings on reach, dose and retention. The focus groups will be facilitated by our research team therapists and qualitative researcher and recorded for qualitative analysis. At the end of the intervention period, all findings will be synthesised to achieve the final intervention for testing in the definitive RCT.

### Progression criteria

Table 2 illustrates the feasibility outcomes that will be used to determine whether the study meets the criteria for progressing to a definitive RCT. The targets were pragmatically established in consultation with the funder and Programme Steering Committee to ensure they align with the potential success of a subsequent RCT.

### Planned outcomes for a definitive RCT

In this single-arm feasibility study, we will collect data on the outcome measures proposed for use in a future definitive RCT (Table 3). This will enable us to test whether the data can be collected, but data will be presented descriptively only. It is possible that some outcome measures will be changed as part of revision of the study prior to undertaking the definitive RCT.

**Table 3 Tab3:** Planned future RCT outcomes

Measure	Description	Time point
**Proposed primary**		
Activities of daily living (ADL) with the Disability Assessment for Dementia (DAD) [41]	This will be assessed by the DAD which has a 40-item scale and address a range of functional domains. 17 items address basic ADLs and 23 items relate to Instrumental ADLs. Scores range from 0–100% witch higher percentage scores representing greater competence in ADLs	Baseline, 6 months
**Secondary**		
Activities of daily living (ADL)	As described above for primary outcome	Baseline, 3 months
Mobility	This will be assessed using the Timed Up and Go (TUG). Participants stand up and walk 3 m, turn around and walk back. The time taken to complete it is recorded. The test is scored as time in seconds	Baseline, 3 months, 6 months
Delirium persistence or recurrence	This will be assessed by DSM5 criteria [42], with some additional enhancements including use of the Informant Assessment of Geriatric Delirium scale (I-AGeD) [43]	Baseline, 3 months, 6 months
Attention	Assessment of attention using months of the year backwards. Participants will be asked to recite the months of the year backwards from December to June, and a score ranging from 0–7 represents number of months successfully recited before failure. A score of 7 indicates correct recital	Baseline, 3 months, 6 months
Level of arousal	Observational Scale of level of Arousal (OSLA) [44] will be used to assess the level of arousal in people with delirium	Baseline, 3 months, 6 months
Cognition	This will be assessed with mini ACE (Mini-ACE) [45] which consists of 5 items and has a maximum score of 30	Baseline, 3 months, 6 months
Verbal fluency	Verbal fluency will be assessed using the ‘Animals’ item from the mini-ACE. The score represents the correct number of animals stated in 1 min	Baseline, 3 months, 6 months
Self-continuity	Single item question to assess sense of self-continuity. Scored on a Likert scale (Strongly disagree/disagree/neither agree nor disagree/agree/strongly agree)	Baseline, 3 months, 6 months
Verbal short-term and working memory	This will be assessed with the Digit span test (Forward Digit Span and Reverse Digit Span). Participants repeat a sequence of numbers in forward or reverse order. The length of digit span repeated correctly will be scored 0–8	Baseline, 3 months, 6 months
Mood assessment	This will be assessed using Geriatric Depression Scale-4 (GDS-4) [46]. The 4 binary item scale will be used which has been validated in older people and people with dementia. The items will be summed to form a total score with a potential range of 0–4	3 months, 6 months
Wellbeing	This will be assessed using the ICEpop CAPability measure for Older people (ICECAP-O) [47]	Baseline, 3 months, 6 months
Residence category	Residence types (own home, living with family, assisted living/warden supported, care home without nursing, care home with nursing or other residence type)	3 months, 6 months
Patient health-related quality of life (HRQL)	This will be assessed using the EQ-5D-5L and EQ-5D-5L proxy [39]. Participant responses to the EQ-5D-5L will be converted to health state values (HSVs) to provide quality-adjusted life-years (QALYs)	Baseline, 3 months, 6 months
Patient HRQL	This will be assessed with the DEMQOL and DEMQOL-Proxy [48]	Baseline, 3 months, 6 months
Carer burden	This will be assessed using the Zarit Burden Interview 12 (ZBI-12) [49]. 12 Items (rated 0–4) are summed to give a total score in the range 0–48	Baseline, 3 months, 6 months
Carer quality of life	This will be assessed using the EQ-5D-5L. Carers participating in this study will be asked to report their own HRQOL, using the EQ-5D-5L, as described above	Baseline, 3 months, 6 months
Carer wellbeing	This will be assessed using the ICEpop CAPability measure for Adults (ICECAP-A) [50]	Baseline, 3 months, 6 months
Resource use	Data will be collected via a proxy Resource Use Questionnaire (RUQ). The RUQ will be informed by the ‘CORE Items for a Standardised Resource Use Measure (ISRUM)’ [37] and the Database of Instruments for Resource Use Measurement [38], and will be designed in collaboration with the PPIE group	Baseline, 3 months, 6 months

### Adverse events management

A risk assessment has identified that this is a low-risk intervention study. Non-serious adverse events (AEs) will not be recorded. We will record serious adverse events (SAE) only for the participants with delirium. All deaths (from any cause) and hospitalisations due to falls, fractures or musculoskeletal injury will be recorded as SAEs. Other SAEs will not be recorded. This rationale is based on several factors, including the expected frequency of other SAEs in the frail population under study and the potential burden that recording these events may impose without providing significant informative insights relevant to the study objectives.

SAEs will be reported to the study sponsor. Events which are unexpected and causally related to the intervention—termed related unexpected SAEs (RUSAE)—will be reported to the research ethics committee and the programme steering committee within 7 days of the sponsor being made aware of the event. Research staff at sites will review the participants’ medical records before each 3-month and 6-month follow-up visit and record all events that are reportable SAEs in the study EDC system. Research staff conducting follow-up visits will also ask participants whether any reportable SAEs have occurred.

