### Study governance

#### Programme Steering Committee

A Programme Steering Committee (PSC) will provide independent oversight for the study, ensuring it is conducted according to the standard set out by the UK Policy Framework for Health and Social Care Research. A separate data monitoring committee will not be convened for this study. The PSC will fulfil the role of a study steering committee and data monitoring committee and will review data completeness, data quality and accumulating safety data at agreed intervals throughout the study.

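### The blanket rule against recording other SAEs leaves no route for a non-fatal, related and unexpected SAE outside the short list to be recorded, assessed or reported

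*Protocol article*

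**What the plan says.** All of the core text is in the protocol article under Adverse events management. The study is classed as low risk. For participants with delirium, "All deaths (from any cause) and hospitalisations due to falls, fractures or musculoskeletal injury will be recorded as SAEs". Below that threshold, "Non-serious adverse events (AEs) will not be recorded", and above it, "Other SAEs will not be recorded". The reasons given include "the expected frequency of other SAEs in the frail population under study and the potential burden that recording these events may impose".

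The next paragraph creates a class of related unexpected SAEs (RUSAEs): "Events which are unexpected and causally related to the intervention". These go to the research ethics committee and the Programme Steering Committee (PSC) within 7 days of the sponsor learning of the event.

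Two checks are described. Site research staff look through the "medical records before each 3-month and 6-month follow-up visit and record all events that are reportable SAEs", and at those visits they ask participants about reportable SAEs.

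Three other sections bear on the point:
- Under Embedded process evaluation, those delivering the sessions "will complete a CRF at each intervention session to document the activities undertaken by the participant", together with any problems in completing the session and the time spent.
- Under Data management, SAE data are entered straight into the electronic data capture (EDC) system and do not pass through paper forms.
- Under Programme Steering Committee, the PSC also acts as the data monitoring committee and "will review data completeness, data quality and accumulating safety data at agreed intervals throughout the study".

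**The concern.** The two paragraphs on adverse events do not fit together. The first decides by category which serious events exist as data. The second makes a commitment defined by relatedness and unexpectedness, and it names no category. For a non-fatal event outside the list, the first paragraph removes what the second would need.

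The intervention is broader than the list. Its six elements, set out under Intervention development, include emotional support and cognitive rehabilitation as well as physical rehabilitation, and the home assessment includes a medication review with possible GP referral. Apart from death, the list covers injury only. A serious event that arose through another element, or a non-injury admission following physical activity, would not be recorded even if the delivery team thought the intervention had caused it.

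What is at stake is the oversight commitment. There is no separate data monitoring committee. The PSC and the ethics committee are the bodies that would act on unexpected related harm, and they cannot be told of an event that the plan says is not recorded.

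**Working it through.** The article gives no figure for this point. Its only design calculation, the confidence interval under Sample size calculation, plays no part here. The check is a trace of each type of event through the written rules, followed by a timeline.

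**Trace of events through the rules**

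| Event in a participant with delirium | Recorded? | Covered by records review and question? | Can be judged related and unexpected? |
|---|---|---|---|
| Death, any cause | Yes | Yes | Yes |
| Admission of a listed kind | Yes | Yes | Yes |
| Any other non-fatal SAE, unrelated or expected | No | No | Not needed |
| Any other non-fatal SAE, related and unexpected | No | No | No route described |

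The fourth row is the gap. Both checks are limited to reportable SAEs, so they inherit the category filter and cannot act as a backstop.

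The stated reasons apply to the third row. Frequent background events in a frail population are a burden to log and tell little. An event in the fourth row is by definition not expected background, so neither reason reaches it.

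**Timeline to the first scheduled check**

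Inputs:
- The home assessment takes place 0 to 2 weeks after discharge, with sessions over the following 12 weeks (Intervention).
- The 3-month visit is timed from discharge, plus or minus 2 weeks (Follow-up).

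Steps:
1. 3 months = 3 × (365.25 / 12) / 7 = 13.04 weeks. The window is 13.04 − 2 = 11.04 to 13.04 + 2 = 15.04 weeks.
2. A full course ends at 0 + 12 = week 12 to 2 + 12 = week 14.
3. Wait from the first home contact to the visit: contact at week 0 gives about 11 to 15 weeks; contact at week 2 gives 11.04 − 2 to 15.04 − 2, about 9 to 13 weeks. The overall range is about 9 to 15 weeks.
4. Share of a 12-week course elapsed at the earliest permitted visit: 11.04 / 12 = 92% if the home assessment is at week 0, and (11.04 − 2) / 12 = 75% if it is at week 2.
5. If the home assessment and the visit are each spread uniformly over their windows (an assumption), the share of visits before a full course ends is (1 + 12 − 11.04) / 4 = 1.96 / 4 = 49%, where 1 is the mean week of the home assessment and 4 is the width of the visit window in weeks.

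The first scheduled check therefore falls late in treatment or just after it. The 7-day clock starts at sponsor awareness and does not shorten this wait.

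**The case against.** Four arguments stand on the other side.

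*The restriction is a reasoned choice.* A low-risk, non-drug feasibility study may limit SAE recording, and the article gives its reasons. The list takes in all deaths and the injury admissions most plausibly linked to strength, balance and functional practice. This stands, and the short list can stay.

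*RUSAE may mean only the related unexpected subset of the SAEs already recorded.* That reading is possible, because the term follows directly on the paragraph that fixes what is recorded. It removes the formal contradiction but not the gap: a related unexpected event outside the list still goes unrecorded, now by intention.

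*An article condenses the full protocol.* This carries weight for timing. The text describes scheduled checks without saying that they are the only route, and event-driven notification is commonly left to the full document. Delivery teams are also offered review sessions with the core team every 3 weeks, where an event could surface. The argument does not help with the category filter, because there the article makes a positive statement.

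*Little would be learned about rates.* With no events in 60 participants, the two-sided 95% upper limit is 1 − 0.025^(1/60) = 6.0%, and no progression criterion in Table 2 depends on SAE counts. This is correct. The case for change rests on reporting individual unexpected harms and not on estimating their frequency. The resource use questionnaire may show some admissions, but it is not described as leading to any relatedness judgement.

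**Conclusion.** The point holds for one class of event: non-fatal, related and unexpected SAEs outside the listed admissions. As written, the chance that such an event is recorded is zero by rule. How many there would be cannot be derived from the document, which gives no rates. The conclusion assumes that the article reproduces the recording rule faithfully, including the absence of any exception. It should be fixed before results are relied on for safety, but it does not threaten the feasibility objectives.

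The delay of about 9 to 15 weeks is secondary. It applies only if the full protocol has no event-driven reporting.

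A reader might infer three stronger claims that the document does not support:
- *Safety data arrive only after treatment.* The 3-month window (about weeks 11 to 15) overlaps the end of a full course (weeks 12 to 14), and the PSC sees accumulating data during the study. If recruitment is staggered, which is not stated, earlier participants' data could reach it while later ones are still being treated.
- *The recorded set leaves out most kinds of harm.* Nothing in the article allows that share to be worked out.
- *The RUSAE rule cannot work at all.* It works for deaths and listed admissions.

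**What to change.** Keep the short list for routine recording and add one exception to Adverse events management, for example: *any other SAE that the site or delivery team considers possibly, probably or definitely related to the intervention will also be recorded and reported*. Word the records review and the participant question to match, so that reportable SAEs include these events. State that RUSAEs are drawn from this wider set.

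The cost is a sentence, two matching edits and a small added reporting load. Unrelated background events remain unrecorded, so the stated concern about burden is respected. Research staff already have the medical records open for the listed events.

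Optional: add a prompt at delivery sessions for a death, an admission or a possibly related serious event since the last contact, passed promptly to the site research team. That team should make the entry in the EDC system, since SAE data do not go through paper forms. The prompt gives delivery staff a safety-reporting task and so needs a line in their training. It is unnecessary if the full protocol already provides for event-driven reporting. The 3- and 6-month checks stay as the backstop.

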### Sample size calculation

As a single-arm feasibility study, the aim is not to determine the effectiveness of the intervention, but rather to estimate key feasibility parameters to inform the design of a subsequent definitive randomised trial. As a result, no formal power calculation has been undertaken to determine the required sample size. Instead, the aim is to recruit a total of sixty participants to the study. If the value of key feasibility parameters, such as the follow-up rate and the percentage of participants attending at least 60% of the intervention sessions, is 70%, sixty participants will allow estimation of the parameter with a 95% confidence interval of 57 to 81% [51].

### Statistical analysis

Descriptive statistics will be used to summarise demographic and outcome data. Continuous data will be reported as means and standard deviations, or as medians and interquartile ranges if the data are skewed. Categorical data will be reported using numbers and percentages. A CONSORT flow diagram will be produced to illustrate the flow of participants through the study. The number of participants approached, eligible, consented and recruited, and assessed at baseline, 3 months and 6 months will be reported, along with the number of participants withdrawn or lost to follow-up between each data collection time point. The reasons for ineligibility, eligible participants not being recruited and the reasons for withdrawal where available will also be reported. The feasibility outcomes (e.g., percentage followed up at 6 months) will be reported with 95% confidence intervals overall and separately for participants with and without dementia. A comprehensive statistical analysis plan will be developed, refined and reviewed by both the trial management group and the programme steering committee before receiving final approval from the statistician and chief investigator, prior to commencing the analysis.

### Data management

Data will be collected onto paper CRFs and entered into a secure online study EDC system, with the exception of SAEs data which will be recorded directly into the EDC system. Data entered into the EDC system will be accessed by authorised personnel only. Audio-recordings of interviews and intervention sessions will be transcribed, transferred using a secure file transfer system and stored on restricted-access folders on secure University of Exeter servers accessed only by authorised members of the study team. Study documents will be archived for 5 years after the end of the study. After 5 years, all personally identifiable data will be securely destroyed upon authorisation from the Sponsor. The anonymised quantitative dataset will be stored indefinitely for the purposes of future ethically approved research.

